### Strategies to improve adherence to interventions {11c}

Subjects will be regularly followed up every 3 months after randomization by phone call or office visit to improve adherence. The drug table will be checked on site or by photos sent from subjects through message service. Blood tests and/or electrocardiograms will be performed every 3 to 6 months to monitor any abnormities.

### Relevant concomitant care permitted or prohibited during the trial {11d}

Subjects with ischemic symptoms will be admitted to the hospital. Repeat interventions were performed if lesions with restenosis were revealed. DAPT will be stopped if any BARC type 3 or 5 bleeding events occur and relevant care will be provided.

#### Follow-up

All randomized subjects will be followed up for 24 months after randomization. The subjects who are randomized to the prolonged DAPT arm will receive a daily dose of a P2Y12 inhibitor and aspirin for a total of 3 years (± 1 month). The other subjects will receive aspirin alone. All subjects will be contacted at 3, 6, 9, 12, 15, 18, 21, 24, 27, 30, 33, and 36 months through a phone call or office visit. Demographic, clinical, and procedural information at the time of enrollment as well as subsequent clinical endpoints, serious adverse events, concomitant medications, and antiplatelet therapy compliance will be obtained. Data will be continuously collected until the end of the study. All endpoints and events that occur after randomization will be adjudicated by an independent clinical events committee who is blinded to the study.

### Provisions for post-trial care {30}

The study will provide post-trial care and insurance for those who suffer harm from trial participation.

### Outcomes {12}

The primary endpoint of this study is the incidence of the composite endpoint, including all-cause death, any MI, and all revascularizations (major adverse cardiac events, MACEs) 24 months after randomization. MIs will be classified and adjudicated according to the Academic Research Consortium (ARC) definitions [16].

The secondary endpoints of the study include the device-oriented composite endpoint (DoCE) of TLF (cardiac death, target vessel-related myocardial infarction [TV-MI], or ischemia-driven target lesion revascularization [ID-TLR]), target vessel failure (TVF; cardiac death, MI, or ischemia-driven target vessel revascularization [ID-TVR]), the individual component endpoints of these endpoints, and scaffold thrombosis. Scaffold thrombosis will be defined as acute (< 24 h), subacute (1 to 30 days), late (30 days to 1 year), and very late (beyond 1 year), and the level of evidence (definite or probable) will be based on the ARC definitions [16].

Bleeding events are the secondary endpoint. BARC type 3 or 5 bleeding events at major bleeding events will include fatal bleeding, intracranial hemorrhage, cardiac tamponade, any transfusion with overt bleeding, a reduction in hemoglobin greater than 3 g/dl, and bleeding requiring surgery (excluding dental, nasal, skin, and hemorrhoid surgeries).

### Participant timeline {13}

The first enrollment is anticipated in the Autumn of 2022. It will take 2 years for all sites to complete enrollment. The time schedule of enrollment, interventions, assessments, and visits for subjects is shown in Fig. 2 below.

**Fig. 2 Fig2:**
[figure not shown]
The schedule of enrolment, interventions, and assessments

### Sample size {14}

Sample size was calculated by the primary endpoint of MACEs. The rates of MACEs related to the XINSORB BRS at the 1- and 3-year follow-ups were 2.5 and 4%, respectively, in the XINSORB RCT. The data were obtained from a randomized controlled study. The patients were relatively low risk. The lesions treated with the XINSORB BRS were simple to moderately complex. The rate of MACEs is definitely higher in the real-world population than in this patient population. However, the incidences of MACEs at 1 and 3 years in the ABSORB China study were 3.8 and 6.4%, respectively [17, 18]. The incidence of MACEs at 3 years in the ABSORB trials (ABSORB II, ABSORB Japan, ABSORB China, and ABSORB III) was 21.0% [3]. Assuming that the incidences of MACEs in the SPARTA trial will be 3.5% for the prolonged DAPT arm and 6.5% for the standard DAPT arm at 3 years, we will need a sample size of 649 subjects per arm to reveal a difference between the two arms by survival analysis based on a Cox model. We anticipate that 80% of subjects will be followed up for 36 months, and the randomization of 1624 subjects (812 per arm) will provide 80% power to demonstrate the superiority of prolonged (36 months) to standard (12 months) DAPT, with a 1-sided alpha value of 2.5%. Assuming that 12% of subjects who are initially enrolled will not be eligible for randomization at 12 months postprocedure because of any event or withdrawal, we need to enroll approximately 2106 subjects treated with XINSORB BRSs at the time of scaffold implantation.

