## Statistical analysis

### Statistical analysis of primary and secondary outcomes {20a}

All analyses will be performed on the intention-to-treat (ITT) population. The primary and secondary endpoints that are related to the time to an event will be assessed with Cox survival analysis. The primary analyses will compare the time to event from 12 to 36 months postprocedure between subjects randomized to 36 and 12 months DAPT using the stratified log-rank test. Kaplan‒Meier estimates of MACEs and other endpoints, as well as the 2-sided 95% confidence interval (CI) of the treatment difference in Kaplan‒Meier rates, will be presented for each treatment arm. Other secondary endpoints will be analyzed with the chi-square test or Fisher’s exact test for frequent comparisons. The two-sided significance level will be fixed at 5%. All tests will be performed with SAS version 9.4 (SAS Institute Inc., Cary, North Carolina, US).

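### At one-sided 2.5%, 649 followed subjects per arm give about 70–73% power for 3.5% versus 6.5%, not 80%, so the power stated for 1624 randomised is wrong

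*Protocol article*

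**What the plan says.** The calculation is in the protocol article, Sample size {14}. It assumes MACE incidences of "3.5% for the prolonged DAPT arm and 6.5% for the standard DAPT arm at 3 years". From these it concludes "we will need a sample size of 649 subjects per arm to reveal a difference between the two arms by survival analysis", with a Cox model as the basis. It then allows for loss: "We anticipate that 80% of subjects will be followed up for 36 months". On that basis, "the randomization of 1624 subjects (812 per arm) will provide 80% power" for superiority, at a one-sided alpha of 2.5%.

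Statistical analysis {20a} names a stratified log-rank test and Cox analysis in the ITT population and says "The two-sided significance level will be fixed at 5" percent. For a superiority test this is the same critical value (1.960) as one-sided 2.5%, so the two sections agree on alpha. Allocation is 1:1 (Intervention description {11a}).

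**The concern.** The section prints every input of the calculation: rates, alpha, power, loss and N. The reader can therefore redo it, and the result is not 649. The step from 649 to 812 is entirely the allowance for 20% loss (649/0.80 = 811.25, rounded up), so 649 is the number that has to carry the 80% power. If it does not, the power claimed for the trial's only superiority hypothesis is false on the plan's own assumptions. A real effect of the assumed size would be missed more often than the stated 20%. No interim analysis of MACE is planned ({21b}), and the sample size section gives no event target that would reveal a shortfall during the trial.

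**Working it through.** **Inputs** (all from Sample size {14} unless noted): p1 = 0.035, p2 = 0.065; one-sided alpha 2.5%, z = 1.960; power 80%, z = 0.8416; 1:1 allocation ({11a}); 80% followed up. The rates are taken as risks over the 24 months after randomisation, the period that the primary analysis covers.

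**Step 1. The plan's own chain.** 649/0.80 = 811.25, rounded up to 812; 2 × 812 = 1624. In reverse, 812 × 0.80 = 649.6. The inflation step is correct; the starting figure is in question.

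**Step 2. Effect size.** HR = ln(0.965)/ln(0.935) = 0.530; |ln HR| = 0.6347. Mean event probability = (0.035 + 0.065)/2 = 0.05.

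**Step 3. Number needed at the stated alpha and power.**
- Schoenfeld: events = 4 × (1.960 + 0.8416)² / 0.6347² = 77.9, so 78. Per arm: 78/(2 × 0.05) = 780.
- Two proportions, unpooled: n = (1.960 + 0.8416)² × (0.035 × 0.965 + 0.065 × 0.935) / 0.03² = 7.849 × 0.09455/0.0009 = 824.6. The pooled form gives 828.
- Arcsine gives 810 and Freedman 840 (84 events).

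The most favourable of these needs 780, about 20% more than 649.

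**Step 4. Where 649 does appear.** Unpooled two-proportion formula:

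| One-sided alpha | Power | n per arm |
|---|---|---|
| 2.5% | 80% | 824.6 |
| 5% | 80% | 649.5 |
| 2.5% | 70% | 648.4 |

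The protocol does not say which formula was used. The second row suggests that the one-sided 5% critical value was used by mistake, but this is an inference.

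**Step 5. Power at one-sided 2.5%.**
- Schoenfeld, 649 followed per arm: events = 2 × 649 × 0.05 = 64.9; power = Φ(√(64.9/4) × 0.6347 − 1.960) = Φ(0.597) = 72.5%.
- Two proportions, unpooled, 649 per arm: Φ(0.03/√(0.09455/649) − 1.960) = Φ(0.526) = 70.0%.
- Freedman, 649 per arm: 69.6%. Simulated log-rank test: 70.4%.

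| Scenario | Events | Power |
|---|---|---|
| 812 per arm, the lost 20% count for nothing (649 followed) | 64.9 | 70–73% |
| 812 per arm, the 20% lost evenly over 24 months and counted until loss (81.2 × 0.9) | about 73 | 75–77% |
| 812 per arm, no loss at all | 81.2 | 79–82% |

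**The case against.** The strongest reply is that the 80% is attached to 812 randomised per arm, not to 649. In an ITT log-rank analysis, subjects who are lost still count until they are censored. This is fair, and it moves the realistic figure from 70–73% to about 75–77%, a shortfall of 3–5 points. It does not restore 80%, which 812 per arm reaches only with complete follow-up, and the same sentence assumes 20% loss.

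A second reply is that other numbers in the article are larger. Sample size {14} enrols 2106 and expects 12% not to reach randomisation. That leaves 2106 × 0.88 = 1853 randomised and 741 per arm fully followed, with power of 76–78%, or about 80–82% with partial follow-up credited. Eligibility criteria {10} says that 2106 will be enrolled and randomised; on that reading about 842 per arm would be followed and power would be about 81–83%. So the trial may in practice come near 80%. But the section ties its power to 1624, and that statement remains wrong. The mismatch between 1624 and 2106 (1624/0.88 = 1846) is a related but separate point.

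A third reply is that the 3-year rates may be cumulative from implantation. Randomised subjects are event-free at 12 months, so a shared first-year rate would have to be removed, which widens the contrast and lowers the required number. With an assumed first-year rate of 2.5% (the XINSORB RCT figure), Schoenfeld needs only about 312 per arm. Something near 649 appears only with a first-year rate of about 0.7% (655 per arm), well below the 2.5% and 3.8% that the section quotes. With 3.8%, the first-year rate alone would exceed the assumed 3-year rate of 3.5%. This reading would change the size and direction of the discrepancy, but it does not explain 649.

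**Conclusion.** The concern holds. At one-sided 2.5% and 80% power, the stated rates require about 780 (Schoenfeld) to 840 (Freedman) followed subjects per arm. None of the standard formulas checked gives 649. With 1624 randomised and 20% loss, power is about 70–73% if lost subjects contribute nothing and about 75–77% if they contribute until they leave. The chance of missing the assumed effect is therefore about 27–30%, or 23–25% on the kinder reading, instead of 20%.

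This rests on 3.5% and 6.5% being risks over the randomised period, on proportional hazards, and on 1:1 allocation. The error concerns a stated design property. It introduces no bias and does not affect the type I error rate.

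**What to change.** Recompute Sample size {14} at one-sided 2.5%, name the formula, say over which period the two rates apply and how loss is counted, and state the event target (78 by Schoenfeld for 80% power). Then choose one of two lines:

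- **Keep 1624 randomised** and state the power as about 72%, rising to about 77% if partial follow-up is credited. Alternatively, state the hazard ratio detectable with 80% power: with 65 events, exp(−2 × 2.8016/√65) = about 0.50.
- **Keep 80% power** and raise the number randomised: 780/0.80 = 975 per arm (1950 in total) by Schoenfeld with no credit for lost subjects, or 828/0.80 = 1035 per arm (2070) by pooled two proportions. With partial follow-up credited, Schoenfeld needs about 870 per arm (1740).

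Neither 649 followed nor 1624 randomised with 20% loss should be presented as giving 80% power at this alpha. The enrolment figure should follow from whichever randomised number is kept.

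The first option costs only wording and a less favourable power statement. The second costs more patients. The article's Trial status section says that the study has not begun, so a correction at that stage is cheap.

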### Eligibility criteria {10}

Study subjects diagnosed with stable, unstable ischemic coronary disease or myocardial infarction (MI) planning to undergo percutaneous coronary intervention (PCI), and no contradiction to prolonged DAPT are eligible for this trial. All subjects will provide written informed consent to participate. Subjects will be enrolled in the study after 12 months (± 1 month) of the DAPT post index procedure. Subjects will be randomized to either discontinue a P2Y12 inhibitor (clopidogrel or ticagrelor) (12 months total) or receive a P2Y12 inhibitor for an additional 24 months (36 months total). Aspirin will be maintained throughout the entire study and can be replaced by cilostazol or indobufen if subjects are intolerant. The dosage of antiplatelet drugs will be determined according to the local standard of practice. Subjects will be treated with the XINSORB BRS only. Figure 1 shows the consort flow diagram of the study.

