**Fig. 1 Fig1:**
[figure not shown]
Consort flow diagram

The major exclusion criteria included (1) cardiogenetic shock; (2) chronic heart failure with a left ventricular ejection fraction less than 30%; (3) subjects on warfarin or similar oral anticoagulation therapy; (4) known allergy or intolerance to aspirin, any P2Y12 inhibitor, heparin, contrast media, sirolimus, PLLA, or other allergens; (5) malignancies and other comorbid conditions with a life expectancy less than 5 years; (6) subjects treated with both BRS and DES; and (7) subjects who planned to receive staged PCI. Given the special properties and sizes of the BRSs, lesions with a reference vessel diameter of 2.75 to 3.5 mm will be included. Lesions located in the left main artery or less than 3 mm to the ostium of the left anterior descending (LAD) artery, the left circumflex (LCX) artery, or the right coronary artery (RCA) and bifurcation lesions (Medina 1,1,1) planning to be treated with two stents strategy will be excluded. The inclusion and exclusion criteria are detailed in Table 1.

**Table 1 Tab1:** Inclusion and exclusion criteria

Inclusion criteria	(1). Subjects who received the XINSORB BRS and were then treated with DAPT for 12 months
	(2). Written informed consent obtained from the subjects
	(3). Candidates qualified for coronary bypass surgery
	(4). Lesions with a reference vessel diameter of 2.75 to 3.5 mm
Exclusion criteria	(1). Age ≤ 18 years
	(2). Cardiogenetic shock
	(3). Chronic heart failure with a left ventricular ejection fraction ≤ 30%
	(4). Oral anticoagulation therapy
	(5). Known allergy or intolerance to the study medications
	(6). Malignancies and other comorbid conditions with a life expectancy less than 5 years
	(7). Subjects treated with both BRS and DES during the index procedure
	(8). Pregnant women
	(9). Planned to receive staged PCI
	(10). Contemporaneous enrollment in a different clinical trial
	(11). Any revascularization within 1 year
	(12). Planned surgery necessitating the discontinuation of antiplatelet therapy within 36 months after enrollment
	(13). Unprotected left main artery
	(14). Lesions located at the ostium of the main coronary artery
	(15). Bifurcation lesions (Medina 1,1,1) planning to be treated with the two stents strategy

A total of 2106 subjects will be enrolled and randomized at approximately 30 centers in China in this manufacturer-run postmarketing study.

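### The enrolment target of 2106 does not follow from 1624 randomized and 12% attrition, which give 1846, and the protocol contradicts itself on how many are randomized and when subjects enter

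*Protocol article*

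**What the plan says.** All references are to the protocol article.

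**Sample size {14}** builds the number in three steps:
- A base size from the assumed event rates: "we will need a sample size of 649 subjects per arm to reveal a difference between the two arms".
- An allowance for incomplete follow-up: "We anticipate that 80% of subjects will be followed up for 36 months", and hence "the randomization of 1624 subjects (812 per arm) will provide 80% power".
- An allowance for loss before randomization: "Assuming that 12% of subjects who are initially enrolled will not be eligible for randomization at 12 months postprocedure", and hence "we need to enroll approximately 2106 subjects treated with XINSORB BRSs at the time of scaffold implantation".

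**Eligibility criteria {10}** reads differently. The sentence after Table 1 states: "A total of 2106 subjects will be enrolled and randomized at approximately 30 centers in China". On timing, the opening text states: "Subjects will be enrolled in the study after 12 months (± 1 month) of the DAPT post index procedure". Inclusion criterion 1 in Table 1 agrees with that later entry, since it requires the 12 months of dual antiplatelet therapy (DAPT) to have been received already.

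The **Abstract (Methods)** and **Intervention description {11a}** fit the earlier entry point. They describe a procedure, then 12 months of DAPT as an observational period, then 1:1 randomization of those who remain free of the listed events. Section {11a} also requires compliance with DAPT.

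**The concern.** The number 2106 is the trial's headline sample size, and it appears in the Abstract, in Eligibility criteria {10} and in Sample size {14}. A reader who follows the last step of the derivation does not arrive at it. The protocol also gives two different numbers to randomize, 1624 and 2106, and two different moments at which a subject becomes enrolled.

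The number randomized is what the power statement rests on. Sample size {14} gives no target number of events, and Interim analyses {21b} plans no interim look at the primary endpoint. The entry point decides whether the 12% allowance belongs in the calculation at all, what the first box of the participant flow contains, and what the 2-year enrolment period in Participant timeline {13} refers to.

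**Working it through.** **Inputs (all from Sample size {14}):** 649 per arm; 80% followed for 36 months; 1624 to be randomized; 12% of those enrolled not randomized; 2106 to be enrolled.

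**Step 1: reproduce the follow-up allowance.** n per arm = 649/0.80 = 811.25, rounded up to 812. Total = 2 × 812 = 1624. This matches the protocol and shows its method, which is to divide by the fraction retained.

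**Step 2: apply the same method to the 12%.** Enrolled = 1624/(1 − 0.12) = 1624/0.88 = 1845.5, so 1846. The protocol states 2106.
- Difference: 2106 − 1846 = 260, and 260/1846 = 14%.
- Multiplying up instead of dividing gives 1624 × 1.12 = 1819, which is further from 2106.

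**Step 3: work back from 2106.**
- Attrition needed to go from 2106 to 1624: 1 − 1624/2106 = 22.9%, against the stated 12%.
- Number randomized if 2106 are enrolled and 12% are lost: 2106 × 0.88 = 1853, which is 229 more than 1624.

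**Step 4: set the two sections side by side.**

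| Point | Sample size {14} | Eligibility criteria {10} |
|---|---|---|
| Number randomized | 1624 | 2106 |
| Entry to the study | At scaffold implantation | After 12 (± 1) months of DAPT |
| Role of the 12% loss | Between enrolment and randomization | None, because it precedes enrolment |

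The two columns cannot both hold. If subjects enter at implantation and some drop out before randomization, the number enrolled and the number randomized must differ. If they enter after 12 months, the loss has already happened and should not inflate the enrolment figure.

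**The case against.** The strongest defence is that the two-stage design is described coherently in the Abstract and in Intervention description {11a}, and that the enrolment number is 2106 wherever it is given. On that view the statement in Eligibility criteria {10} that 2106 are also randomized is loose drafting, and enrolment there may mean entry to the randomized phase. Figures 1 and 2, which were not available for this review, may show the entry point clearly. This is fair as to intent, and it means that wording can resolve the contradictions. It does not repair the arithmetic, and calling the number approximate does not cover a 14% gap.

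Three stronger readings are tempting, and the document does not support them.
- **That the slip costs power.** It does not: 2106 is more than the stated inputs need. A separate calculation from the stated rates ("3.5% for the prolonged DAPT arm and 6.5% for the standard DAPT arm at 3 years") does suggest less than 80% power at 1624 with 80% followed. That shortfall comes from the base size of 649, not from the attrition step.
- **That there are three competing randomization targets.** The protocol states two, 1624 and 2106. The figure of 1853 is only what 2106 implies at 12% loss.
- **That a 30% loss to follow-up was used in place of 20%.** This can be made to land on 2106 by rounding to the nearest integer (649/0.70 = 927; 927/0.88 = 1053; 2 × 1053 = 2106). No 30% loss is stated, and the protocol's own step rounds up. Another unstated chain also comes close: applying the 12% twice gives 1624/0.88/0.88 = 2097. The origin of 2106 cannot be determined from the text.

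**Conclusion.** The enrolment figure is wrong as written. With 1624 randomized and 12% lost beforehand, the protocol's own method gives 1846. The stated 2106 is 260 subjects (14%) higher and corresponds to 22.9% attrition. Separately, Eligibility criteria {10} contradicts Sample size {14} on the number randomized (2106 against 1624). With Table 1 criterion 1, it also contradicts Sample size {14}, the Abstract and Intervention description {11a} on when subjects enter.

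The consequence is an unsupported target and an ambiguous number to randomize, not a loss of power.

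The figure 1846 is conditional on the 1624, and so on the 649 per arm, which does not reproduce at the stated one-sided 2.5% and 80% power. The hazard ratio from the two rates is ln(0.965)/ln(0.935) = 0.530. The Schoenfeld formula then needs 4 × (1.960 + 0.842)²/(ln 0.530)² = 78 events. At a mean event rate of 5% that is 78/0.05 = 1560 subjects, or 780 per arm. A comparison of two proportions gives 828 per arm. This is a separate question, but it bears on whether enrolment should be lowered.

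**What to change.** 1. State one chain and one entry point in Sample size {14}: number enrolled at implantation, × 0.88 randomized at 12 months, × the stated follow-up fraction.
2. Choose one of two consistent versions:
   - 1846 enrolled for 1624 randomized; or
   - 2106 enrolled, with either the attrition rate restated (22.9% if 1624 is kept, with a justification) or the expected number randomized restated (about 1853 at 12%).
3. Re-check the 649 per arm at one-sided 2.5% before choosing the version that reduces enrolment, because 1846 inherits any error in it.
4. In Eligibility criteria {10}, remove the statement that the 2106 are also randomized. Align the time of enrolment in the text and in Table 1 criterion 1 with Sample size {14}, keeping criteria for entry separate from criteria for randomization.
5. Define completion of accrual by the number randomized.

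The cost is wording in Sample size {14}, Eligibility criteria {10} and Table 1, and in the Abstract if 2106 changes. Trial status says that the study had not begun, so on the document's account the correction comes before any subject is recruited. No extra subjects are needed on account of this point alone.
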